### Procedures

After randomization and formation of a regional intervention team, participating professionals of all eight hospital regions will be sent the baseline questionnaire by email. This will be repeated 3 and 12 months after the training (intervention regions) or the inclusion of the first patient (control regions). A physician or nurse with knowledge of the study will check all COPD-patients admitted to the pulmonology care department due to an acute exacerbation, and their informal caregiver if applicable, for eligibility. After the informed consent procedure, participating patients and informal caregivers complete the questionnaires required for the Propal-COPD tool and the baseline questionnaires during the hospital stay. A physician or nurse will enter the Propal-COPD tool indicators and baseline characteristics in an online data management system. The system automatically calculates the Propal-COPD score, based on the published algorithm [16]. For a patient of the intervention region, the score will be displayed as “positive” or “negative” and in the control regions it will be displayed as “xxx”. A patient with a positive Propal-COPD score and, if present, his or her participating informal caregiver, will be sent follow-up questionnaires 3 and 6 months after inclusion. Questionnaires will be sent on paper or digitally via email, depending on personal preference. A flowchart of the cluster randomized controlled trial is shown in Fig. 3.

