### Participants

#### Healthcare professionals

Each participating hospital region forms an intervention group consisting of at least one of the following professions: pulmonologist, respiratory nurse of pulmonology care department, palliative care consultant in the hospital, general practitioner specialized in asthma and COPD, general practitioner specialized in palliative care, consultants from the regional palliative care consultation teams. The following professionals can be involved facultatively if present in that region: respiratory nurse in primary care, pulmonologists in training, practice nurse and other relevant professionals.

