### Recruitment of regions

To recruit hospital regions for participation, invitational letters will be sent to the heads of departments of respiratory medicine of all hospitals in the Netherlands. After agreement to take part in the study, eight hospital regions will be selected for randomization to the intervention or control group. Participating regions will be offered a small reimbursement of expenses (maximum €2.5 K per region).

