### Randomization

Hospital regions will be randomly allocated by an independent statistician to the intervention or control condition, stratified by the number of COPD exacerbation hospital admissions per year.

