### Blinding

To minimize response bias, patients and informal caregivers will not be told whether their hospital is assigned to the intervention or control group. Also, the researcher will be blinded during the analysis process of effect outcomes, using recoded identification numbers of participants. Blinding of professionals for cluster group allocation will not be possible due to the nature of the implementation strategy and intervention. However, professionals of control regions will be blinded for the Propal-COPD score. As a consequence, it remains unknown to them which patients take part in the effectiveness study and receive follow-up questionnaires.

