### Secondary effect outcomes

Secondary effect outcomes will be spiritual well-being, disease-specific health-related quality of life, unplanned healthcare use, date and place of death if applicable, informal caregiver burden and professionals’ self-efficacy and role identity with providing palliative care and discussing end-of-life. Satisfaction with care will be assessed at the patient, informal caregiver and professional level. The measurement instruments to be used are detailed in Table 2.

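### The professionals' baseline questionnaire is sent after randomization to staff who cannot be blinded, so the between-arm comparison of professional outcomes is open to post-randomization selection

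*Protocol article*

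**What the plan says.** Regions are approached through their heads of department. Under Recruitment of regions: "After agreement to take part in the study, eight hospital regions will be selected for randomization to the intervention or control group". Under Randomization: "Hospital regions will be randomly allocated by an independent statistician to the intervention or control condition". The unit that agrees and is allocated is the region.

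On team membership, the Healthcare professionals section says "Each participating hospital region forms an intervention group consisting of at least one of the following professions", and adds for further professions "The following professionals can be involved facultatively if present in that region". It gives no upper limit and no rule for choosing individuals.

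On timing, Procedures says "After randomization and formation of a regional intervention team, participating professionals of all eight hospital regions will be sent the baseline questionnaire by email". On knowledge of allocation, Blinding says "Blinding of professionals for cluster group allocation will not be possible due to the nature of the implementation strategy and intervention".

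Secondary effect outcomes include professionals' "self-efficacy and role identity with providing palliative care". Table 2 schedules these, together with professionals' satisfaction with care and self-reported delivery of core elements, at iT0, iT3 and iT12. Analysis of effect evaluation compares the arms at professional level with multilevel mixed models under intention-to-treat, and adjusts for baseline imbalance where needed.

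**The concern.** In a cluster trial, randomization protects the comparison of individuals only if they are identified without regard to allocation. Here the professionals are both participants and reporters of their own outcomes, and their baseline is collected once allocation can be known. Three things could then differ by arm before any training takes place: who joins the team, who returns iT0, and how respondents rate their own competence.

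What is at stake is the causal reading of the professional results. Self-efficacy is among the secondary outcomes listed in the abstract. Self-reported delivery of core elements also feeds the implementation score, and the Discussion relies on comparing that score between arms to deal with possible dilution of the treatment contrast. An analysis plan written later cannot recover a pre-allocation baseline that was never collected.

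**Working it through.** The point turns on the order of events, so the check sets the sections side by side. The plan gives no figure to reproduce.

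1. **Fixed before allocation:** the region's agreement (Recruitment of regions). No list of named staff is mentioned.
2. **Allocation:** by region, by an independent statistician (Randomization).
3. **Knowledge of allocation:** professionals cannot be blinded (Blinding). No section describes withholding allocation from them until iT0 has been returned.
4. **Discretion over membership:** a minimum set of professions, optional additions, individuals chosen by the region (Healthcare professionals). Table 1 lists forming the group as the first component of the implementation strategy, and Implementation outcomes reports team composition as part of the strategy's reach. The protocol itself thus treats composition as something tied to the intervention.
5. **Baseline:** iT0 follows both randomization and team formation (Procedures).
6. **Use:** a between-arm comparison of these self-reports (Analysis of effect evaluation).

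The Procedures sentence says that randomization and team formation both precede iT0. It does not strictly say which of the two comes first.

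| Reading | Joining | Returning iT0 | Self-rating at iT0 |
|---|---|---|---|
| Randomize, form team, send iT0 | open to influence | open to influence | open to influence |
| Form team, randomize, send iT0 | protected | open to influence | open to influence |

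The first reading is the natural one and fits the Table 1 entry. Under the second the problem is narrower, but it remains.

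**What adjustment can do.** Let p be the share of an arm's respondents who differ because of allocation, and d their mean difference in the follow-up outcome in SD units. The unadjusted shift is p × d. Adjusting for iT0 score, function, experience and education removes the part of d that those variables explain, but not unmeasured motivation. Separately, if knowing the allocation shifts iT0 self-ratings in the intervention arm by s, adjusting for iT0 with slope b carries −b × s into the adjusted difference. The document gives none of p, d, s or b, so no size follows.

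**The case against.** The strongest reply is that the arms are more alike than the concern suggests. Every region must supply the same required professions, and several of those roles are narrow, which limits the choice of individuals. The Control section offers control professionals similar training and toolbox access once recruitment is complete, so the incentive to join differs mainly in timing. The Discussion says that all regions, control regions included, had a particular interest in the topic. Baseline scores are collected, Baseline measures adds function, years of experience, palliative care experience and education, and adjustment is provided for. All of this stands and lowers the risk. It leaves unmeasured motivation, differential response and the effect of known allocation on self-rating.

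A reader might infer more than the document supports:

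- **That no staff list existed before allocation.** The article describes none, but silence in a condensed article is not proof, and the professional timeline figure is not available here.
- **That control staff only fill in questionnaires.** The deferred training contradicts this, and so does the screening and data entry by a physician or nurse, for which Procedures makes no exception for control regions.
- **That team membership stays open until training session 2.** The decision there about who should be involved concerns steps of the regional action plan, and need not mean enrolment as a questionnaire respondent.
- **That a bias in SD units can be quoted.** Every input would have to be invented.

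**Conclusion.** The point holds as a risk, not as a demonstrated bias. The timing of iT0 after randomization is explicit, and so is the impossibility of blinding professionals. Two assumptions remain: that allocation is in practice known to staff when they answer iT0, which follows naturally from those two statements, and, for the part about joining, that teams form after randomization.

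The effect is confined to professional-reported measures: self-efficacy, role identity, satisfaction with care and delivered core elements. A reader might extend it to the main result, but FACIT-Pal is reported by patients and is not reached by this route. The direction and size of any bias cannot be determined from the document. The existing safeguards are partial, and the limitations in the Discussion do not mention this one. It is an inexpensive improvement worth making and does not threaten the trial's primary conclusion.

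**What to change.** Re-order steps that all eight regions already carry out:

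1. After a region agrees to take part, it names its team.
2. That team completes iT0.
3. Only then is the statistician's allocation disclosed to the region.
4. Professional outcomes are analysed on this pre-allocation roster, adjusted for iT0 score, with later joiners reported separately.

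The cost is a short delay, because disclosure waits for rosters and questionnaires from hospital, primary-care and regional staff. No extra measurements are needed. The change does not address unblinded self-report at iT3 and iT12, which should be stated as a remaining limitation.

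The Discussion refers to control regions as already randomized, so allocation may have been disclosed. In that case, report team composition and iT0 response by arm, identify professionals who joined later, and describe the professional comparison as open to selection.

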#### Patients

Patients diagnosed with COPD and admitted to the hospital for an acute exacerbation will be invited to participate in the study. Patients not able to complete questionnaires in Dutch, patients with severe cognitive decline (e.g. dementia) and patients on the waiting list for lung transplantation will be excluded. After completion of the baseline questionnaire, patients will be screened using the Propal-COPD tool [16]. Patients with a positive Propal-COPD score will be included in the effectiveness study. The Propal-COPD tool consists of seven indicators: Medical Research Council (MRC) dyspnea score of 5, Clinical COPD Questionnaire (CCQ) score > 3, forced expiratory volume in 1 s lower than 30% predicted, presence of specific comorbidities, body-mass index lower than 21 kg/m2 or weight loss (> 10% in the last 6 months or > 5% in last month), previous hospitalization for acute exacerbation in the last 2 years (last 2 years ≥2 admissions or last year ≥1 admission), and a negative answer to the surprise question (“Will you be surprised if your patient would die in the next coming 12 months?”) [16]. For each indicator, specific weight is given, together generating a total score. A score exceeding the previous published cut off value of − 1.362 corresponds with a high probability for death within 1 year, which is considered a proxy for having palliative care needs.

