**Implementation strategy**		
***Components***	***Content of the component***	***Tools/materials/ underpinning theory***
Formation of regional intervention group	Multidisciplinary regional team	Implementation strategies integrated into multiple settings and directed to multiple professions involved are more effective [17]
Access to online toolbox	Website with information and guidance on the core elements of palliative care in COPD, including tools and links for facultative use	Quality Framework [7] Input from experts
Training session 1 (3 h)	Introductory information on the project and research	n.a.
	Instruction the Propal-COPD tool to identify the palliative phase in patients with COPD	Propal-COPD tool [16]
	Multidimensional assessment (physical, psychological, social, spiritual)	Adapted version of Problems Square [18]
	Communication training on advance care planning in COPD including roleplay with actors	Training in palliative care communication with roleplay supports implementation [19–21]
	Non-pharmacological and pharmacological dyspnea management	Breathing Thinking Functioning model [22]
Training session 2 (3 h)	Discussion current palliative care as organized in region vs. desired palliative care	7-phase model [23]
	Introductory information on implementing care pathway	7-phase model [23]
	Filling in formats A to E (who does what how and when) leading to first draft of regional action plan	Flowchart on patient care process (see Fig. 2)
	Assigning local implementation leaders	7-phase model [23]
Completion of regional action plan	Agreement on who does what how and when	Format regional action plan Action planning stimulates behavior change [24] and assures the suitability of the intervention to the existing structure of the region
Monitoring	Monitoring meetings on site	Audit and provide feedback to monitor, evaluate, and modify provider behavior [25]
	Evaluation meetings with local implementation groups	Share local knowledge on how implementers and clinicians made something work in their setting and then share it with other sites [25]

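### The surprise question, which helps decide entry to the effectiveness study, is answered after randomisation by staff who know the allocation, and instruction and feedback on the tool are described only for the intervention arm

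*Protocol article*

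**What the plan says.** In the Procedures section allocation comes first: "After randomization and formation of a regional intervention team, participating professionals of all eight hospital regions will be sent the baseline questionnaire by email". The Blinding section accepts that "Blinding of professionals for cluster group allocation will not be possible due to the nature of the implementation strategy and intervention". Patients are then found locally. "A physician or nurse with knowledge of the study will check all COPD-patients admitted to the pulmonology care department due to an acute exacerbation", and once consent is given, "A physician or nurse will enter the Propal-COPD tool indicators and baseline characteristics in an online data management system". The system computes the score from a published algorithm with one fixed cut-off.

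The Patients section makes the score the gateway: "Patients with a positive Propal-COPD score will be included in the effectiveness study". Among its seven weighted indicators is "a negative answer to the surprise question", that is, the clinician would not be surprised if the patient died within a year. The item's weight is not given.

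Two things differ between arms while patients are being recruited:

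- **Instruction.** Table 1 lists, in training session 1 of the implementation strategy, "Instruction the Propal-COPD tool to identify the palliative phase in patients with COPD". The Control section offers control staff comparable training only when recruitment is finished.
- **Feedback.** Control staff see only a masked value (xxx), whereas intervention staff see the result. Procedures puts it this way: "For a patient of the intervention region, the score will be displayed as “positive” or “negative” and in the control regions it will be displayed".

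The analysis is by intention to treat with multilevel mixed models. Baseline variables are adjusted for only if an imbalance is found (Analysis of effect evaluation). FACIT-Pal is collected at baseline, 3 and 6 months (Table 2).

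**The concern.** In a cluster trial that recruits after randomisation, comparability of the arms depends on applying the same entry rule in the same way on both sides. Here the rule is identical on paper, but one of its inputs is a prognostic judgement made by people who know the arm. In intervention regions they have been taught the tool, they learn the outcome of each rating, and a positive result starts the palliative pathway. In control regions the result has no consequence for care and is not seen.

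If that leads to different answers for similar patients, the two arms analyse different populations. Intention-to-treat keeps included patients in their allocated arm; it does nothing about who was included. A difference in case mix would then be read as an effect on 6-month quality of life, or would hide one. The Discussion mentions the uncertain proportion of positive patients and the tool's robustness, but not differential enrolment.

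**Working it through.** **1. Can allocation reach the entry decision?** The order is: regions randomised, staff aware of allocation, eligibility check, consent and baseline questionnaire, indicators entered by staff, score computed, positive patients included. Every step after the first takes place with allocation known locally. The surprise question is the item that depends most on personal judgement.

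**2. What do the stated safeguards reach?**

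| Safeguard (section) | Protects | Leaves open |
|---|---|---|
| All exacerbation admissions checked (Procedures) | Who is considered | Who is approached and consents; the surprise answer |
| Baseline questionnaire before screening (Patients) | Baseline FACIT-Pal answers | The surprise answer |
| Automatic score, fixed cut-off (Procedures, Patients) | The classification rule | The inputs to it |
| Patients not told the allocation (Blinding) | Patient-reported answers | Staff-rated items |
| Adjustment if imbalance is seen (Analysis) | Possibly the estimate | Which variables, and when |

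None of them has the surprise question rated by someone unaware of allocation, or gives both arms the same instruction beforehand.

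**3. The plan's own figures, to set a scale.** Inputs from Sample size calculation: difference 9, SD 25, two-sided alpha 0.05, power 80%, ICC 0.01, 10% loss, eight regions.

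- Per group: 2 × [25 × (1.960 + 0.8416) / 9]² = 121.1, against 121 stated.
- Total: 242 × [1 + (30.25 − 1) × 0.01] / 0.9 = 242 × 1.2925 / 0.9 = 347.5, against 347 stated. The cluster size 242/8 = 30.25 is assumed; the article does not state it.

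Standard error of the arm difference with 347 enrolled: completers 347 × 0.9 = 312.3; per region 312.3/8 = 39.04; design effect 1 + 38.04 × 0.01 = 1.380; effective number per arm 156.15/1.380 = 113.1; SE = 25 × √(2/113.1) = 3.32 points.

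**4. Illustration (assumed inputs, no covariate adjustment).** Let a share s of one arm be included only because the item was answered differently, and let those patients differ by g FACIT-Pal points. The shift is B = s × g, of either sign. With no true effect, the chance of a significant result is Φ(−1.96 + B/SE) + Φ(−1.96 − B/SE).

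| s | g | B (points) | B/9 | Chance of a false positive |
|---|---|---|---|---|
| 5% | 5 | 0.25 | 3% | 5.1% |
| 10% | 10 | 1 | 11% | 6% |
| 20% | 10 | 2 | 22% | 9% |
| 30% | 20 | 6 | 67% | 44% |

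The documents give neither s nor g, and s cannot be worked out without the item's weight. The table shows a scale and is not an estimate.

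**The case against.** The best counter-argument is that staff do not choose who is included. An algorithm does, and the other six indicators (MRC dyspnoea score, CCQ, FEV1, comorbidities, BMI or weight loss, previous admissions) are largely measured, recorded or reported by the patient. This stands. A reader might infer that unblinded staff control inclusion as a whole; the text supports only a route through one subjective item and through the approach to patients for consent.

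Second, a case-mix difference should show in baseline FACIT-Pal, and the plan allows adjustment. This also stands in part. But the article makes adjustment depend on an imbalance being noticed and does not commit to baseline FACIT-Pal. Patients who differ in prognosis need not differ only on that scale.

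Third, identification with the tool is listed in Table 1 as a component of the intervention, so intervention staff have to be taught it and see the result. That explains the asymmetry without removing its effect on enrolment.

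Fourth, a condensed article may omit short data-entry guidance for control staff. That is fair: the article describes none and does not exclude it.

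A reader might also infer that masking the score in control regions makes entry conditions less alike. The documents do not show this. The masking has a stated purpose, which is to keep control staff from knowing who is followed up. The result also appears only after that patient's score has been calculated. What is left is feedback that could influence ratings of later patients, and possible re-entry of items, on which the article is silent.

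**Conclusion.** The point holds in a limited form. As written, the plan lets one subjective entry item be answered under different instruction and feedback in the two arms by staff who know the allocation, and no stated safeguard closes that route. The order of steps, the raters, the training and the display are all set out in the article, so this is not a detail left to an unseen document.

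The size is unknown. A shift of 1–2 points rests on assumed shares of 10–20% and an assumed 10-point gap, before any adjustment; adjustment for baseline FACIT-Pal would reduce it. At that scale the false-positive rate would be about 6–9% instead of 5%, so the matter deserves correction but does not undermine the design.

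The direction is also unknown. A reader might infer that trained staff would answer 'not surprised' more readily, bring in less ill patients and so favour the intervention. The documents do not support that step: training could equally make the answers more accurate, and nothing in the text says which way they would move.

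**What to change.** 1. **Sensitivity analysis.** Prespecify a repeat of the primary analysis restricted, in both arms, to patients who remain Propal-positive when the score is recomputed with the surprise item at its non-risk value. Membership of that set does not depend on the surprise answer, and the indicators are already in the data system.
2. **Adjustment.** Replace adjustment conditional on observed imbalance with prespecified adjustment for baseline FACIT-Pal in the primary model. Add the remaining Propal indicators as covariates in a supporting model.
3. **Data system.** Lock the entered indicators before the result is displayed.

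The cost is one system setting and a few lines of analysis plan, with no new data. The restricted analysis will have fewer patients and lower precision; how many fewer cannot be estimated without the item's weight, so it should support the primary result and not replace it. These steps do not address differences in who is approached or consents, nor learned feedback from earlier patients.
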